### **Relationship with the drug**

The physician will use the following definitions to establish the causal relationship of each AE:

|                    |                                                                                                                                                                                                                             |
|--------------------|-----------------------------------------------------------------------------------------------------------------------------------------------------------------------------------------------------------------------------|
| Probably related   | The adverse event has a clear temporal relationship with the drug or recurs on drug rechallenge, and other cause is unlikely or significantly less likely.                                                                  |
| Possibly related   | The adverse event has a marked temporal relationship with the drug and is equally likely or less likely that another cause exists as compared to the possible relationship with the study drug.                             |
| Probably unrelated | The adverse event has a minimal or no temporal relationship with the drug or another more likely cause exists, or both.                                                                                                     |
| Unrelated          | The adverse event is due to an underlying or concomitant disease or to the effect of another drug, and is not related to the drug (e.g. has no temporal relationship to the drug or another much more likely cause exists). |

### **Adverse event collection period**

SAEs will be reported from signature of informed consent and up to 30 days after the last dose of medication as described below. The same reporting procedure should be followed for any late SAE (occurring after this 30-day period) that is possibly or probably related to study medication.

### **Serious adverse event reporting**

If a SAE occurs, whether or not related to the investigational drug, the investigator will report to the Sponsor by telephone or fax any serious adverse events occurring during the study, regardless of their causal relationship, within 24 h of awareness of the event or in the next working day. The investigator must expedite report to the sponsor any SAEs that are fatal or life-threatening:

**[contact]**

**[contact]**

All SAE reports by telephone must be followed by the corresponding written report form within 48 hours. For fax reports, the investigator will record the information referring to the SAE in the relevant form.

The minimum initial information for reporting an adverse event should include the following:

- adverse event description and onset date.
- patient code, sex, and age.
- information about the treatment received.
- name and address of the reporting physician.
- whether or not a causal relationship to the study drugs is considered to exist.

If death of a participating subject has been reported, the investigator will provide the Sponsor and CRECs involved with any additional information requested.

The form for reporting SAEs to the sponsor is enclosed as Appendix 4.

The Sponsor is responsible for reporting all suspected SUSARs within the times established by the applicable Spanish regulations to:

- The Spanish Agency for Medicinal Products and Medical Devices (AEMPS)
- The Clinical Research Ethics Committee (CREC) involved in the trial for SUSARs occurring in participating subjects from the sites of their area of influence.
- The relevant bodies of the autonomous communities when the suspected SUSAR has occurred in the healthcare centers of the corresponding region.
- The principal investigators.

The Sponsor also agrees to report to the pharmacovigilance department of the marketing authorization holders of the study drugs in Spain any serious or unexpected adverse events according to the reporting procedures.

Appendix D, provided by the AEMPS in the clarifications on the application of the clinical trial regulations from May 1, 2004 (version no. 4, 30 November 2006), will be used for reporting SUSARs to the CRECs and regulatory authorities.

## **9.2. MANAGEMENT OF TOXICITY:**

All clinically significant laboratory toxicities will be managed according to the ACTG classification of adverse event severity (version 1.0 December 2004) (Appendix 5).

## **10. ETHICAL ISSUES**

### **10.1 GENERAL CONSIDERATIONS**

This study will be performed in compliance with the principles established in the Declaration of Helsinki and its subsequent revisions (Appendix 2) and the applicable Spanish regulations on clinical trials.

The study will be conducted according to the ICH Good Clinical Practice guidelines.

An insurance policy has been contracted for the study with the company HDI Hannover Internacional (España) Seguros y Reaseguros, S.A., in compliance with the provisions in Royal Decree 223/2004.

### **10.2 OBTAINING INFORMED CONSENT**

Before any study-specific procedure is performed, the patient will be informed about the nature of the study treatment and will be provided with any relevant information about the intended objectives, potential benefits, and potential adverse events. The procedures to be followed and the potential risks will be explained to the patient. The patient must read and sign the approved informed consent form. Once signed and dated by the patient and the investigator, the patient will be given a copy of the signed informed consent. The patient may withdraw from the study at any time, without this affecting his or her future medical care. The patient information sheet and informed consent for the study is enclosed as Appendix 3.

## **11. PRACTICAL CONSIDERATIONS**

### **11.1 RESPONSIBILITIES OF STUDY PARTICIPANTS**

#### **11.1.1. Rules for the patient**

The patient must follow the instructions of investigators and report any events to them.

The patient will be duly informed of any prohibitions or restrictions to be respected during the study. Non-compliance with these recommendations will result in study withdrawal.

Patients may terminate their participation in the study at any time.

#### **11.1.2. Rules for the investigating staff**

The investigator agrees to comply with the rules set forth in the applicable clinical trial regulations: Medicines Act 2006 (Official State Journal no. 178, 27.07.06) and Royal Decree 223/2004 on Clinical Trials.

## **11.2 DATA MANAGEMENT AND FILE**

The management, reporting and transfer of personal data from all participating subjects will comply with the Spanish Personal Data Protection Act 15/1999, of December 13.

On enrolment, each patient will be assigned a patient number, that will be recorded in the CRF.

Copies of all relevant information will be kept by the investigator and Sponsor in accordance to the provisions in Article 17 of Directive 2005/28/EC for at least 5 years after study completion or for a longer time if so required by the applicable local regulations or any agreement between the Sponsor and the Investigator.

The investigator will be responsible for keeping adequate information about each patient so that regulatory authorities may have access to such information if required. These records should be kept confidential for the time period legally established in the applicable regulations.

## **11.3 PUBLICATION CONDITIONS**

The sponsor will review all requests for publication of the results of this study. The sponsor recognizes the importance of dissemination of results and therefore agrees to their partial or total disclosure by the principal investigators, provided the manuscript has previously been approved by the sponsor. The sponsor may require changes considered necessary for ensuring quality and protecting intellectual property. The principal investigator understands and agrees that, under certain conditions, publication of results will have to be delayed to ensure the scientific quality and integrity of data; for instance, until results are available in a number of sites representative of the study. The principal investigator understands and agrees that the sponsor has the right to decide the exact time when data may be disclosed. By signing this protocol, the principal investigator accepts the terms of the publication policy of the sponsor and agrees to abide by them.

## **11.4 PROTOCOL AMENDMENT PROCEDURE**

Any protocol change should be documented in writing as an amendment.

Amendments should be duly identified by their chronological order number, and dated and signed by the sponsor and investigator.

If changes are relevant, the sponsor must request approval from the reference CREC and AEMPS, as set down in the applicable regulations.

The sponsor will be responsible for keeping a log of any changes that do not meet the criteria for a relevant amendment, as required in the applicable regulations, and monitor their implementation at the trial sites. Such log should be available in the event of an inspection or audit.

### **11.5 CLINICAL RESEARCH ETHICS COMMITTEE (CREC)**

The protocol and informed consent form will be reviewed by a duly formed CREC. The decision of the CREC on the study conduct will be provided to the investigator in writing; a copy of this decision should be provided to the sponsor. The CRECs of participating centers will also assess the patient information sheet and the suitability of the investigating staff of their own hospitals.

The sponsor will submit the required study progress reports to the CREC and will report any suspected unexpected serious adverse reactions. At the end of the study, the sponsor should report them to the CREC.

## **12. STATISTICAL ANALYSIS**

The primary analysis of the study will be performed at the end of the 6 months of follow-up in all patients.

### ***Sample size and rationale***

In a similar study population (e.g. HIV+ patients with an undetectable viral load, i.e. < 50 copies/mL of HIV-1 RNA), the mean baseline quality of life score measured with the MOS-HIV questionnaire was 61.84 [24]. As standard deviation is not available, we assume for all calculations that standard deviation will be the highest score minus the lowest score in the quality of life dimension (e.g. 100) divided by 5, which gives 20. This standard deviation of 20 is the same as found in HIV-infected asymptomatic patients, patients with AIDS-related symptoms, or patients with AIDS and a CD4 cell count <100 [25]. Assuming, then, that quality of life will remain unchanged in patients assigned to the control group (maintaining current antiretroviral therapy) and will improve by 10% (e.g. to scores of 68.02) in patients assigned to the experimental group (LPV/r® as monotherapy), with a 1:2 ratio, an 80% statistical power, and a two-sided alpha of 0.05, 372 patients would be required, 248 randomized to the experimental group and 124 randomized to continue on the current antiretroviral therapy.

Assuming 7% follow-up losses, the final sample size required will be of 260 patients for the experimental group and 130 patients for the control group, i.e. a total of 390 patients.

Because the triple antiretroviral therapy based on a PI boosted with ritonavir (control treatment) has been widely studied for a practical sense, it has been considered to allocate the sample to twice the experimental treatment (1:2, respectively) [24 ], [26].

This distribution of the sample (1:2) compared with the distribution of equal groups (1:1) ensures greater security in the contrast of the study to a possible greater variability of response in the quality of life in the experimental group since this group is expected to more patients with diarrhea to begin new therapy. [27]

Also it will provide an improved accuracy in estimating mean and smaller confidence intervals, for example, more than 1% in the estimated proportions near 50%.

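### The planned 390 patients allow for 4.6% losses, not the stated 7%, and the claim that 1:2 allocation secures the between-arm contrast does not follow from the assumed common SD of 20 (minor)

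*Protocol*

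**What the plan says.** Everything at issue stands in Protocol section 12, under Sample size and rationale.

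- **Effect and SD.** Control patients are assumed to stay at a mean MOS-HIV score of 61.84, while quality of life "will improve by 10% (e.g. to scores of 68.02) in patients assigned to the experimental group". No SD was available from the source, so the plan takes "the highest score minus the lowest score in the quality of life dimension (e.g. 100) divided by 5, which gives 20" and applies that one value to all calculations.
- **Evaluable number.** "with a 1:2 ratio, an 80% statistical power, and a two-sided alpha of 0.05, 372 patients would be required", split as "248 randomized to the experimental group and 124 randomized to continue on the current antiretroviral therapy".
- **Loss allowance.** "Assuming 7% follow-up losses, the final sample size required will be of 260 patients for the experimental group", with 130 controls. The total of 390 is repeated in the Synopsis (item 13) and in section 6.1.
- **Reasons for 1:2.** Three are given. First, the control regimen has already been widely studied. Second, compared with equal groups, 1:2 is said to ensure more security in the contrast, given that quality-of-life responses may vary more in the experimental arm. Third, "Also it will provide an improved accuracy in estimating mean and smaller confidence intervals", illustrated by a gain of more than 1% for proportions near 50%. The third reason names neither an arm nor a between-arm difference.

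**The concern.** The evaluable number, the loss rate and the enrolled number are stated together, and they cannot all hold. Someone monitoring the trial would take 7% as the loss it can bear with power intact, when the margin is used up at 4.6%. Section 12.1 (A.2) itself expects more withdrawals for diarrhoea in the experimental arm, so the allowance is a figure that may be called on.

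The second reason for 1:2 compares it directly with 1:1 and concerns the contrast, which is the trial's primary comparison. With equal SDs and a fixed total, equal groups give the most precise difference. The stated benefit therefore runs against the plan's own SD assumption unless the experimental arm is considerably more variable. At stake is whether readers believe that the allocation strengthens the comparison when, on the stated assumptions, it costs some precision.

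**Working it through.** **Inputs** (all from Sample size and rationale): difference 68.02 − 61.84 = 6.18; SD 20 in both arms; two-sided alpha 0.05; power 80%; control:experimental 1:2; losses 7%; enrolled 130 + 260 = 390.

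**1. Reproduce the evaluable number.** With k = 2 experimental patients per control,

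n(control) = (1 + 1/k) × (1.960 + 0.8416)² × SD² / difference² = 1.5 × 7.849 × 400 / 6.18² = 123.3, rounded up to 124.

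The experimental arm is 248 and the total 372. This matches the plan exactly. A noncentral-t calculation also gives 124 controls (power 80.0%).

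**2. Apply the loss allowance.**

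| Step | Result |
|---|---|
| 372 / (1 − 0.07) | 400 |
| 372 × 1.07 (cruder inflation) | 398.0 |
| 372 × 1.05 | 390.6 |
| Loss that 390 absorbs: (390 − 372)/390 = 18/390 | 4.6% |
| By arm: 12/260 and 6/130 | 4.6% each |

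Neither usual method gives 390 from 7%. An inflation of about 5% does.

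**3. Power if 7% are lost.** 390 × 0.93 = 362.7, or about 121 + 242. Then

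SE = 20 × √(1/120.9 + 1/241.8) = 2.228; 6.18/2.228 = 2.774; 2.774 − 1.960 = 0.814; power = Φ(0.814) = 79.2%.

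The t-based figure is 79.0%.

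**4. Allocation and the contrast, at N = 390 and SD 20 in both arms.**

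- 1:2: SE = 20 × √(1/130 + 1/260) = 2.15; 95% half-width 4.21.
- 1:1: SE = 20 × √(2/195) = 2.03; 95% half-width 3.97.
- Ratio 1.061, so the 1:2 interval is about 6% wider.

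Put as patient numbers, 80% power needs 372 at 1:2 and 330 (165 per arm) at 1:1.

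**5. When 1:2 would be tighter.** Let r be the experimental SD divided by the control SD. The 1:2 interval is narrower if 1/130 + r²/260 < (1 + r²)/195. Multiplying by 780 gives 6 + 3r² < 4 + 4r², so r² > 2 and r > 1.41. Against a control SD of 20, the experimental SD would have to exceed 28.3. The plan gives no separate experimental SD.

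**6. Each arm's own interval at N = 390** (95% half-widths, 1:2 against 1:1).

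| Estimate | 1:2 | 1:1 |
|---|---|---|
| Experimental mean | 2.43 | 2.81 |
| Experimental proportion near 50% | 6.08 points | 7.02 points |
| Control proportion near 50% | 8.60 points | 7.02 points |
| Difference in proportions near 50% | 10.5 points | 9.9 points |

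Only the experimental arm's own estimates gain.

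**The case against.** **The loss slip hardly matters.** The gap from 400 to 390 is 2.6%, and the cost is about one point of power. Section 12.4 softens it further: patients who leave are scored at their abandonment evaluation or have baseline carried forward, so many losses stay in the analysis. The ANCOVA also adjusts for baseline, whereas the sample size uses an unadjusted SD. A baseline-to-week-24 correlation of about 0.16 would recover the shortfall (1 − 0.16² ≈ 0.974, against 363/372 = 0.976). This is fair on size, with two limits: the documents give no such correlation, and carried-forward baselines may dilute the effect. It does not make the stated 7% correct.

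**The contrast claim is conditional.** It refers to a possible greater variability in the experimental arm, so testing it at equal SDs tests a case that it is not about. This stands in part. The claim is unsupported rather than the reverse of the truth, because a large enough SD ratio would bear it out. But it is worded as something 1:2 ensures, and the required ratio is neither assumed nor stated.

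**The confidence-interval sentence is right as far as it goes.** A reader might infer that it wrongly promises a narrower between-arm interval. It names no such interval, and its talk of estimating a mean and proportions fits the experimental arm, where it is correct. Near 50% the full width shrinks by 2 × (7.02 − 6.08) = 1.88 points, which agrees with the plan's example. Its fault is only that it does not say where the gain applies.

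**The ratio does not rest on precision alone.** The first reason given is that the control regimen is well studied. The cost of 1:2 is already paid, since 372 was computed at that ratio.

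**Conclusion.** The point holds as a minor one. The stated 7% loss does not lead to 390; the enrolled number covers 4.6%. At a true 7% loss, power is about 79%, assuming the plan's difference of 6.18, SD of 20, an unadjusted comparison, and lost patients contributing nothing. The claim of greater security in the contrast is unsupported by the plan's common SD, under which 1:2 widens the between-arm interval by about 6%.

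Two stronger readings are not supported. A reader might conclude that the trial is materially underpowered; the shortfall is about one point, and the base calculation is sound. A reader might also conclude that 1:2 is a mistake to be replaced by 1:1. It is a trade-off with a separate stated reason, and its cost is included in the 372. Nor does greater variability count against 1:2 in particular: at an experimental SD of 28.3 both allocations have SE 2.48 and about 70% power, so that loss comes from the larger SD and not from the ratio.

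**What to change.** In Sample size and rationale:

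1. Replace the loss statement with: *390 allows for 4.6% losses; at 7% losses power is about 79%.*
2. Remove the claim that 1:2 makes the contrast more secure than 1:1, or qualify it: with a common SD of 20 the between-arm interval is about 6% wider than at 1:1, and 1:2 is tighter only if the experimental SD exceeds about 1.41 times the control SD.
3. Keep the sentence on smaller confidence intervals, but say that the gain applies to the experimental arm's own estimates only.
4. Let 1:2 rest on its first stated reason, that the control regimen has been widely studied.

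The cost is wording only. The enrolled number, allocation, procedures and analysis do not change; the stated loss allowance becomes slightly less favourable.

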#### **Statistical analysis**

Baseline characteristics of study groups will be compared using an analysis of variance (ANOVA). The mean, median, standard deviation, and range will be provided for continuous variables, and the distribution of absolute frequencies and percentages will be given for discrete variables. When required, 95% confidence intervals will be calculated. Discrete variables will be compared using a Chi-square test.

For quality of life analysis, the primary population will include all patients with data available from baseline up to at least one post-baseline visit (e.g. the intention-to-treat population).

In case of patient abandonment is taken as a post-treatment evaluation the one obtained at the time of abandonment. If there is no post-treatment evaluation as a neutral value, baseline observation value will be carried forward until month 24 or the time of abandonment (Baseline Observation Carried Forward).

The main deadline to study results will be week 24 of the study. An analysis of covariance (ANCOVA) will be used for quality of life comparison. The model will include the baseline values for the items in the MOS-HIV questionnaire, age and sex as covariates, in the control and study groups. For primary endpoint analysis, the values in the MOS-HIV and EQ-5D questionnaires in the different weeks as compared to baseline will be provided for each treatment group.

An analysis of covariance (ANCOVA) will be used for comparisons between both treatment groups.

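### The trial is sized on one SD of 20, yet its 1:2 split is defended by possibly greater variability in the larger arm; there an ordinary ANCOVA is conservative and 1:2 rarely helps

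*Protocol*

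**What the plan says.** Protocol section 12, Sample size and rationale, reports that "the mean baseline quality of life score measured with the MOS-HIV questionnaire was 61.84" in a similar population and supposes that quality of life "will improve by 10% (e.g. to scores of 68.02) in patients assigned to the experimental group", with no change in the control group. With no SD available, "we assume for all calculations that standard deviation will be the highest score minus the lowest score in the quality of life dimension", taken as 100 and divided by 5, which gives 20. "with a 1:2 ratio, an 80% statistical power, and a two-sided alpha of 0.05", the result is that "372 patients would be required, 248 randomized to the experimental group and 124 randomized to continue on the current antiretroviral therapy". An allowance for losses brings this to 390.

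The same section gives several reasons for 1:2 allocation. One is that, compared with 1:1, it makes the study's comparison more secure against "a possible greater variability of response in the quality of life in the experimental group", because more diarrhoea is expected among patients starting the new therapy. No experimental-arm SD, SD ratio or power under unequal SDs follows.

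For the analysis, section 12.4 states: "An analysis of covariance (ANCOVA) will be used for comparisons between both treatment groups". The quality-of-life model has baseline MOS-HIV values, age and sex as covariates. Nothing is said about the residual variance structure or the type of standard error, and the section leaves detail to a later statistical analysis plan.

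**The concern.** The section raises unequal variability as a reason for a design choice and then carries it into neither the power calculation nor the named analysis. This matters because of where the extra variance would lie. An ANCOVA in its usual form estimates one residual variance from both arms, weighted by arm size. If the larger arm is the more variable one, that estimate is dominated by the large variance, which is then also applied to the small control arm, where it does not belong. The standard error comes out too large, the interval too wide, and the test rejects less often than its nominal level. Part of any power loss would then come from the choice of standard error alone and could be recovered without enrolling anyone.

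The allocation argument is also at stake. If 1:2 does not protect the comparison in the situation described, the protocol should not rest on that reason.

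**Working it through.** **Inputs from the protocol:** difference 68.02 − 61.84 = 6.18; SD 20; control to experimental 1:2; two-sided alpha 0.05; power 80%; 124 and 248 evaluable. **Assumed here:** control SD 20 and experimental SD 22, 25 or 30, since the protocol gives none. SD 30 is extreme: a uniform spread over 0 to 100 has SD 100/√12 = 28.9.

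**1. The plan's own figure.** n(control) = (1 + 1/2) × 20² × (1.960 + 0.842)² / 6.18² = 600 × 7.849 / 38.19 = 123.3, so 124; experimental 248; total 372. This matches exactly. SE = √(400/124 + 400/248) = 2.200, and power = Φ(6.18/2.200 − 1.960) = 80.2%.

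**2. Unequal SDs.** Let s be the experimental SD.
- True SE = √(400/124 + s²/248).
- Common-variance SE = √{[(123 × 400 + 247 × s²)/370] × (1/124 + 1/248)}.
- True alpha of the common-variance test = 2Φ(−1.960 × common SE / true SE).
- Power, common-variance = Φ((6.18 − 1.960 × common SE) / true SE).
- Power, unequal-variance = Φ(6.18 / true SE − 1.960).

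At s = 25: true SE = √(3.226 + 2.520) = 2.397; pooled variance = 203,575/370 = 550.2; common SE = √(550.2 × 0.01210) = 2.580; ratio 1.076. Alpha = 2Φ(−2.110) = 3.5%. Power = Φ(0.469) = 68.0% against Φ(0.618) = 73.2%.

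| Experimental SD | True SE | Common SE | Ratio | True alpha | Power, common | Power, unequal | Power at 1:1 (186/186) |
|---|---|---|---|---|---|---|---|
| 20 | 2.200 | 2.200 | 1.000 | 5.0% | 80.2% | 80.2% | 84.6% |
| 22 | 2.275 | 2.349 | 1.032 | 4.3% | 75.6% | 77.5% | 80.9% |
| 25 | 2.397 | 2.580 | 1.076 | 3.5% | 68.0% | 73.2% | 74.9% |
| 30 | 2.618 | 2.979 | 1.138 | 2.6% | 55.2% | 65.6% | 64.7% |

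Simulation of 100,000 trials per setting, with pooled and Welch t tests, agrees. At SD 25 it gives alpha 3.5% and 5.0%, and power 67.7% and 72.8%. At SD 20 in both arms, power is 80.2% and 80.1%.

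**3. Is 1:2 safer than 1:1?** At a fixed total N, the variance of the difference is (3·s_C² + 1.5·s_E²)/N for 1:2 and (2·s_C² + 2·s_E²)/N for 1:1. The first is smaller only if s_E² > 2·s_C², an SD ratio above √2 = 1.41 (experimental SD above 28.3). With equal arms the two standard errors coincide, so the last column serves for both. With the common-variance SE, 1:2 has the lower power in every row, for example 68.0% against 74.9% at SD 25.

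**4. Baseline adjustment.** If 20 is the raw-score SD and the baseline correlation ρ is the same in both arms, both residual SDs shrink by √(1 − ρ²). The SE ratio and true alpha in the table do not change; power rises. To regain 80%, ρ must be about 0.25 (unequal-variance SE) or 0.32 (common) at SD 22, 0.39 or 0.49 at SD 25, and 0.54 or 0.64 at SD 30. The protocol gives no ρ.

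**5. All 390 analysed (130/260).** Power starts at 82.0%. Common against unequal-variance power is then 77.6% and 79.4% at SD 22, 70.2% and 75.2% at SD 25, and 57.4% and 67.6% at SD 30.

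**The case against.** The protocol calls the greater variability possible; what it expects is more diarrhoea. A planning SD together with a remark about a possible departure from it is not a contradiction, and the printed 80% is right under its stated assumption. A reader might infer that power falls below 80%, or that the sizing is wrong. The documents do not support that: they give no larger SD, every figure for unequal SDs rests on a value assumed here, and moderate baseline correlation in the planned ANCOVA, for which the sizing takes no credit, could restore 80%. This objection stands and limits the point.

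A reader might also infer a raised false-positive risk. The opposite holds: with the larger variance in the larger arm, the common-variance test is conservative. At SD 22 the choice of standard error costs only about 2 points of power.

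It can further be said that the type of standard error is a matter for the statistical analysis plan, which is not shown and may already specify a robust one. That is fair as far as section 12.4 goes, and silence there is not in itself a fault. It does not reach the sample size section, where the single SD and the variability argument for 1:2 stand together and the second is not borne out by arithmetic.

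Finally, 1:2 has other stated grounds, among them that the control regimen is already well studied. Those are untouched.

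**Conclusion.** The point holds in a limited form. The 372 patients and 80% power are correct for SD 20 in both arms and only then; no shortfall is demonstrated. Under the variance pattern that the protocol itself raises, a common-variance ANCOVA would be conservative, by an amount that depends on an SD the protocol does not give: small at SD 22, about 5 points of avoidable power loss at SD 25, and about 10 at the extreme SD 30. These power figures are for the unadjusted comparison at 124/248 with control SD 20. The overstated standard error carries over to the adjusted analysis for the same ratio of residual SDs.

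The allocation sentence is the weaker part of the text. As a reason to prefer 1:2 over 1:1 for the comparison between arms, it is true only above an SD ratio of about 1.41, and then only with an unequal-variance standard error. Over the range examined, 1:2 with the common-variance analysis has less power than 1:1.

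**What to change.** In section 12.4, keep the ANCOVA and its covariates, but base the standard error, 95% confidence interval and p-value for the treatment difference on a heteroscedasticity-robust (HC3) estimator or on arm-specific residual variances. If the statistical analysis plan already does so, a cross-reference is enough.

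In section 12, state that 80% is conditional on SD 20 in both arms. Withdraw the sentence that 1:2 is more secure against greater experimental-arm variability, or qualify it with the SD ratio above which it is true.

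The cost is a few sentences. The 390 patients, the endpoint and the model stay as they are. If the variances turn out equal, the loss is negligible: 80.1% against 80.2% in the simulation above, with the unadjusted Welch test standing in for the robust analysis.
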